### 5 STUDY SUMMARY

| **Title** | Feasibility evaluation of a smartphone based Cognitive Behavioural Therapy (CBT) intervention for the treatment of low mood or support for worry management in female armed forces veterans in England, Wales, and Scotland. | |
| --- | --- | --- |
| **Internal ref. no. (or short title)** | Iona female veterans | |
| **Clinical Phase** | II | |
| **Trial Design** | Feasibility RCT with acceptability and usability questionnaire  Parallel group design with randomisation conducted using block randomisation (blocks of 3) and the trial is conducted with an exploratory framework. | |
| **Trial Participants** | Female forces veterans | |
| **Planned Sample Size** | 60 (30 participants per group) | |
| **Treatment duration** | 6 weeks | |
| **Follow up duration** | End of 6-week intervention engagement period and 4 week follow up (10 weeks post randomisation) | |
| **Planned Trial Period** | 10 weeks post-randomisation | |
|  | **RCTs & measures** | **Outcome domains** |
| **Primary/Feasibility/Methodological Outcomes** | Consented, recruited, completed screening, recruitment method, measure completion (baseline, 6 weeks, 10 weeks), drop out, drop out reason | Feasibility |
| **Secondary Outcomes** | PHQ-9/GAD7  Work and Social Adjustment Scale (WSAS) | Depression/Anxiety dependent on lower score on outcome measure at baseline determining severity.  Functioning |
| **Acceptability** | Mobile Acceptability and Usability Questionnaire (MAUQ) | Acceptability and Usability |
| **Intervention** | Intervention: IonaFFV for depression engaged with for 6 weeks intervention engagement period  Control: Iona SHAM CONTROL app developed to match engagement time | |
| **Route of Administration** | Iona app (IonaFFV) for the treatment of depression or Generalised Anxiety Disorder | |

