### 8.4 Randomisation scheme

The feasibility RCT will follow MRC Complex Interventions Guidelines and relevant CONSORT reporting requirements with a pre-registered trial protocol. Randomisation will be in blocks of 3 with randomisation to the 2 arms (IonaFFV vs Iona SHAM CONTROL) conducted automatically by Qualtrics survey platform to minimise selection bias and maintain methodological rigor. Following randomisation IonaFFV or Iona SHAM CONTROL will be automatically sent a link to download the app.

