### 8.6 Method of implementing the randomisation/allocation sequence

Participants will be randomised by pseudorandom number generation. Eligible participants will receive an email confirmation which provides a download link and unique participant code to each participant accepted into the trial, and they will be prompted to download the app as soon as possible. Once selected according to the randomisation sequence either IonaFFV or Iona SHAM CONTROL, participants will download the app on their phone. Participants are blinded to the randomisation.

Should a participant fail to download the app and enter the code, an automated sequence of emails at the rate of 1 per day over a 7-day period will be sent to the participant reminding them to do so and reiterating the download and sign-up instructions. After this time no further contact with the participant will be made.

Detailed procedure for randomisation:

1. Participants are randomised in blocks of 3 (30 participants per arm) into the 2 arms (IonaFFV versus Iona SHAM CONTROL) on an intention-to-treat basis.
2. Block randomisation will continue until 60 (30 each arm) are randomised. As eligible participants complete the initial screening and demographics questionnaire they will be randomised in blocks of 3 to either the control or intervention arm by the Postdoctoral Research Associate or the Graduate Research Assistant.

3.       The system will record the allocation and the date randomised.

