### 8.7 Blinding

All follow-up research data will be routinely collected by the UNIEXE Qualtrics system, with the system sending reminders by email and text message. The Lead Researcher will undertake the initial analysis which will be discussed with the wider research team and agreed with the written analysis section by the Trial Steering Committee. Participants and data analysts will be blinded.

[name] (Iona Mind) will provide a set of download codes for group A and group B. The researchers will not know which group of codes contains the access to the intervention or control arm. The researchers will randomly allocate these codes to eligible participants in blocks of 3.

Accidental unblinding may occur if one of the research team receives an email from a participant with questions or comments containing identifiable information about the treatment arm they are in. If this happens, the researcher will notify the research team and will not conduct any analysis to allow the blinded researchers to conduct the analysis.

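### A block size of three cannot be 1:1 over two arms and does not ensure the stated 30:30, and the protocol conflicts on whether software or staff allocate

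*Protocol*

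**What the plan says.** The study summary (section 5) describes the design as "Parallel group design with randomisation conducted using block randomisation (blocks of 3" and gives the sample size as "60 (30 participants per group". Section 6.1 repeats the block size. The detailed procedure in section 8.6 states "Participants are randomised in blocks of 3 (30 participants per arm) into the 2 arms", and then "Block randomisation will continue until 60 (30 each arm) are randomised". No section says how a block of three is divided between the two arms.

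On who allocates, section 8.4 says: "Randomisation will be in blocks of 3 with randomisation to the 2 arms (IonaFFV vs Iona SHAM CONTROL) conducted automatically by Qualtrics survey platform". Section 8.5 says that university researchers randomise, using codes that come from the app company. Section 8.6 has participants "randomised in blocks of 3 to either the control or intervention arm by the Postdoctoral Research Associate or the Graduate Research Assistant". Section 8.7 says: "The researchers will randomly allocate these codes to eligible participants in blocks of 3". Section 8.7 also says that the codes come as group A and group B, and that the researchers are not told which group is the intervention.

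**The concern.** A permuted block balances two arms only if its size is a multiple of two. Sections 5 and 8.6 give an equal target per arm and, next to it, a block size that cannot produce it. Someone building the list would have to invent the missing rule, and different inventions lead to different arm sizes.

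The conflict over the allocator bears on concealment. Section 8.4 rests its protection against selection bias on automatic allocation ("conducted automatically by Qualtrics survey platform to minimise selection bias"). If people hand out the codes instead, that protection no longer applies as described, and a block size printed in the protocol helps them anticipate the next label.

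This matters more here than the small sample suggests. The principal objective (section 3) is to settle methodological uncertainties for a definitive trial, and section 10.7 counts maintained blinding as a feasibility outcome. An undefined randomisation procedure would be carried into the next trial.

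**Working it through.** **Inputs.** Total 60, 30 per arm, two arms (sections 5 and 8.6). Block size 3 (sections 5, 6.1, 8.4, 8.6, 8.7). Block composition: not given, so the readings below are assumptions.

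**Within a block.** 3 / 2 = 1.5 per arm, so no block can be 1:1.

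**Over the trial.** 60 / 3 = 20 blocks. The stated 30:30 depends on how the blocks are filled:

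| Reading of the block | Arm sizes |
| --- | --- |
| Each block 2:1 or 1:2 at random | 20 + Binomial(20, 0.5) in one arm; SD √(20 × 0.25) = 2.2 |
| Whole block of three sent to one arm | 3 × Binomial(20, 0.5); SD 3 × 2.236 = 6.7 |
| Every block 2:1 | 40:20 |
| Exactly ten blocks 2:1 and ten 1:2 | 30:30 |
| Three per arm, so a true block size of six | 30:30 |
| Random 2:1 or 1:2, each arm closed at 30 | 30:30, with forced final allocations |

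For random 2:1 or 1:2 blocks:

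- P(exactly 30:30) = C(20,10) / 2^20 = 184,756 / 1,048,576 = 17.6%.
- P(arms differ by 4 or more) = 1 − (184,756 + 2 × 167,960) / 1,048,576 = 50.3%.
- The central 95% range for one arm is about 26 to 34.

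If each arm is closed at 30, the target is met. In simulation, however, the last 3.9 allocations on average are then fully determined.

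**Precision.** The variance of a difference in means, relative to 30:30, at the edge of that range: (1/34 + 1/26) / (1/30 + 1/30) = 1.018, an increase of 1.8%.

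**Predictability of the next label if staff allocate.** Take a known block size of three and an unknown ratio. The six possible orders are AAB, ABA, BAA, ABB, BAB and BBA.

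- First position: best guess correct 1/2 of the time.
- Second position: 2/3 (after A, two of the three remaining orders have B next, and the reverse after B).
- Third position: after AA or BB (2 of 6 orders) the label is certain; otherwise it is even. Correct 1/3 + (2/3 × 1/2) = 2/3.
- Average: (1/2 + 2/3 + 2/3) / 3 = 11/18 = 61%, against 50% with no information.
- Fully determined: (2/6) / 3 = 1/9 = 11% of labels.

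By the same enumeration, a single known block size of 2, 4 or 6 gives best-guess rates of 75%, 71% and 68%, with 50%, 33% and 25% of labels determined. Predictability therefore comes from a fixed, known size and not from the number three.

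**The case against.** A reader might infer that the trial will miss 30:30. The documents do not support that. It can arise by chance, it follows from two unstated compositions, and the instruction in section 8.6 to continue until each arm has 30 can be read as a cap. What stands is that no rule is stated that secures it, and that the cap has a price in determined allocations.

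A reader might also take 40:20 as the expected result, with 44% of labels determined. Both figures need a constant 2:1 ratio, which contradicts the 30 per arm in sections 5 and 8.6. They are not a fair reading of the plan.

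The most tempting inference is that staff can foresee the arm and select participants accordingly. Three things weigh against it.

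- Section 8.7 masks the code groups, so a guess reaches the label and not the arm.
- Consent and screening are online self-report. First-stage screen-out is automatic (section 8.2), as is registration once criteria are met (section 6.1), so there is little room to act on a guess.
- Section 8.4 has software allocate, so staff allocation is one side of an unresolved conflict.

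These points limit the concern but do not remove it. Section 8.7 concedes that a participant's email may reveal the arm. Section 8.3 makes the Lead Researcher the contact for people who cannot download their app. One revealing message tied to a code group would identify both groups. The remedy in section 8.7 takes that person out of the analysis and says nothing about allocation.

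Finally, the trial is exploratory with no sample size calculation (sections 5 and 11.1), so modest imbalance does little harm. That is accepted.

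**Conclusion.** The protocol is wrong as written on two counts. First, its block size is incompatible with 1:1 allocation to two arms, and no composition is given that secures the stated 30:30. Under random 2:1 or 1:2 blocks the target is met 17.6% of the time; that composition is an assumption. The effect on precision is minor. The fault is that the procedure cannot be carried out from the text. Second, section 8.4 conflicts with sections 8.5, 8.6 and 8.7 on who allocates, and these must be reconciled.

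Weakened concealment is a secondary and conditional point. It applies if staff allocate, amounts to about 61% best guesses and 11% determined labels when the ratio is unknown, and concerns the label unless the A/B key leaks. No claim of actual selection bias is supported.

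**What to change.** In sections 5, 6.1, 8.4, 8.6 and 8.7, replace the block size of three with: *1:1 randomly permuted blocks of varying even size, closing at 30:30*. Keep the sizes in a restricted document. They should not appear in the protocol, which staff read and which section 8.5 says will be put forward for publication. One fixed even size would cure the balance but leave the labels predictable.

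Reconcile sections 8.4, 8.5, 8.6 and 8.7 so that a concealed computer system is the only allocator. Section 8.4 already names Qualtrics. That system should issue the group A and group B codes supplied by the app company, so that the masking in section 8.7 is kept.

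The cost is a wording change, a new allocation list and its set-up in the system, with no added participants or staff. The protocol does not show whether recruitment has begun. If it has, document the block composition and the allocator actually used, and report the achieved arm sizes.

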### 6.1 Participant registration/randomisation procedure

The consent and study screening process will take place on the University of Exeter password protected online Qualtrics system. Female veterans wishing to consider participation will either click on the link or scan the QR code on study advertisement to access the Participant Information Sheet. Contact information for the researcher will be provided on the Participants Information Sheet to enable potential participants to gather more information if requested. Upon receipt of a completed Consent Form, the potential participant is able to access and complete the first screening measures to determine study eligibility. Eligible participants will then be guided to complete the second screening measures to determine study suitability based on participants symptoms of anxiety and depression and well-being – PHQ9 and GAD7. Second screening will also serve as baseline measures for participants. Where inclusion criteria are met, and upon completion of the sociodemographic questions, the participant will be randomised in blocks of 3 into either of the study arms and automatically registered on to the trial. Once randomised, participants will be sent a code to download the app.

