### 6.3 Data protection/confidentiality

### 6.3.1. Data protection

The conduct of the project will comply with GDPR. Adequate measures to ensure data protection and confidentiality will be duly taken into account by the research team. Local and national rules on data protection will be followed, and no personal information of participants will be transferred unless such transfer is essential for the conduct of the trial.

All research data will be stored on a UNIEXE database linked to the unique identifier ID to pseudonymise all information collected. Before taking part, all participants are provided with Participant Information Sheet which also includes information on privacy policy. At initial screening potential participants are not asked to provide their email addresses contact details (i.e., mobile phone number). If participants are eligible to take part after initial screening, they are asked to complete the second screening, which also serves as the baseline measure, sociodemographic questionnaire and provide their email address and mobile phone number. Phone numbers are collected to send reminders to participants. The database contains all the baseline (i.e., second screening) and follow up data collected from the EDC system. The codes linking contact information with the database containing outcomes will be destroyed as early as is legally required (no earlier than all data being archived – 3 months post study endpoint) – data (including participant details and consent) may need to be retained and not deleted for a longer period due to future research indicators that may require researchers to contact the individual or actions taken by participant against the research. This approach has proven successful in prior digital interventions for wellbeing and has been approved by multiple institutional and National Health Service research ethics in the UK; adaptations will be made as necessary for specific local ethical requirements.

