### 8.3 Consent

Potential participants will be initially routed to, or seek out, the UNIEXE Qualtrics page and will be provided with the Participant Information Sheet. If interested in participating, they will select a checkbox that takes them to the Consent Form and data protection policy to review on the trial electronic platform. Study eligibility and inclusion criteria will be clearly stated, and participants asked to electronically sign the Consent Form and date. The Consent Form asks for consent to undertake the initial and secondary screening, taking part in the trial as well as confirmation that the participant understands the nature of the study and meets inclusion criteria. Participants are asked to confirm that they meet each criterion. If eligible, participants will be asked to provide an e-mail address and mobile phone number.

If a participant completes the Consent Form and is eligible for the trial, they will be given an e-mailed confirmation that they are in the study, a unique study participant trial number and instructions indicating how, as per randomisation scheme, to download IonaFFV or Iona SHAM CONTROL on either an Android or Mac (IOS) based mobile phone. They are also provided with contact details (email, and/or telephone number as available) for the Lead Researcher if further study information is wanted or they are struggling to download IonaFFV or Iona SHAM CONTROL.

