### 8.8 Baseline data

Baseline data will be collected after participants sign the consent form but before randomisation. Here, data from second screening, if participants meet the study inclusion criteria, serves as baseline data. This is when the participant completes the PHQ9 and GAD7 on University of Exeter Qualtrics for the first time.

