**Table 9 Assessment Schedule**

| **Procedures** | **Initial screening** | **Baseline (second screening)** | **6 weeks post initial app engagement** | **4 weeks follow-up**  **(10 weeks post initial app engagement)** |
| --- | --- | --- | --- | --- |
| Informed consent | Yes | Yes | No | Yes |
| Demographics | Yes | Yes | No | No |
| Mental Health History | Yes | No | No | No |
| Eligibility assessment | Yes | Yes | No | No |
| Randomisation | No | Yes | No | No |
| Access to intervention | No | No | Yes | No |
| Assessment of wellbeing and depression | No | Yes | Yes | Yes |
| Assessment of current functioning | No | Yes | Yes | Yes |
| Assessment of usability and engagement | No | No | No | Yes |
| Feasibility outcomes | No | No | No | Yes |
| Adverse event assessments | No | No | Yes | Yes |

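### Protocol section 8.6 step 2 triggers randomisation after the initial screening and demographics without requiring the second screening, contradicting sections 6.1 and 8.8 and Table 9

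*Protocol*

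**What the plan says.** Section 8.6 sets out a detailed procedure for randomisation. Its second step gives the trigger: "As eligible participants complete the initial screening and demographics questionnaire they will be randomised". The step names the Postdoctoral Research Associate or the Graduate Research Assistant as the person who allocates. The second screening is not mentioned.

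Table 8 splits the entry criteria into two tiers. Age, service, residence, psychiatric history, medication and access to a smartphone belong to the initial screening. The PHQ-9 limits (5 or more, below 20), the GAD-7 limit (below 15) and the PHQ-9 item 9 limit (at most 1) belong to the second screening, which doubles as baseline.

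Three other places give the order of events:

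- Section 6.1 describes the second screening and then states: "Where inclusion criteria are met, and upon completion of the sociodemographic questions, the participant will be randomised".
- Section 8.8 states: "Baseline data will be collected after participants sign the consent form but before randomisation". It identifies that baseline with the second screening: "This is when the participant completes the PHQ9 and GAD7 on University of Exeter Qualtrics for the first time".
- Table 9 marks randomisation No under initial screening and Yes under baseline (second screening).

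**The concern.** Step 2 is written as an operating instruction, and the check it leaves out is the one that applies the severity and suicide-risk limits. If it were followed literally, three things would be at stake.

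- **Safety.** A woman could be allocated before item 9 of the PHQ-9 had been looked at. Section 13.1.2 says GP details are not held, and section 13.2 says no medical care is provided whatever the level of risk. Screening before allocation is therefore one of the main safeguards.
- **Baseline.** A PHQ-9 or GAD-7 completed after allocation is not the pre-randomisation baseline that section 8.8 promises.
- **Feasibility outcomes.** Numbers screened out and numbers dropping out are both among the primary feasibility outcomes. A woman who is allocated and then found to be outside the limits is a screening failure by nature but a post-randomisation loss in the flow diagram.

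**Working it through.** No formula applies to the order of procedures, and section 11.1 states that there is no sample size calculation. The check is a comparison of the relevant text.

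**1. The two orders**

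| Source | Order |
| --- | --- |
| 6.1 | consent, first screening, second screening, criteria met, sociodemographic questions, randomisation, app code |
| 8.8 | consent, second screening as baseline, randomisation |
| Table 9 | randomisation at the baseline (second screening) column, not at initial screening |
| 8.6 step 2 | initial screening, demographics, randomisation; second screening absent |

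Step 2 omits the second screening. It does not say that randomisation comes before it.

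**2. Does the word *eligible* in step 2 supply the missing check?** Not reliably. Section 6.1 uses the word for women who have passed only the first screening: "Eligible participants will then be guided to complete the second screening measures to determine study suitability". Section 6.3.1 does the same: "If participants are eligible to take part after initial screening, they are asked to complete the second screening". In both places the Table 8 severity and item 9 limits have still to be applied.

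**3. Does the demographics condition supply it?** Only in part. Sections 6.1 and 6.3.1 place the sociodemographic questions after the second screening, which suggests a woman has reached that stage. But Table 9 ticks demographics under initial screening as well. Section 6.3.1 also asks for the second screening, the sociodemographic questionnaire and contact details together, without making the later items depend on the limits being met. Completed demographics therefore do not show that the limits were met.

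**4. Can the software be relied on to enforce the order?** The protocol does not settle who allocates. Section 8.4 says Qualtrics randomises automatically. Section 8.6 step 2 says one of two named staff roles does it, and section 8.7 says researchers allocate the download codes. If allocation is by hand, the wording of step 2 is the control.

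**5. What happens to a woman allocated outside the limits?** Section 8.12 allows participants who did not meet the baseline criteria to be replaced and their data removed, though it does not say whether they had already been randomised. Section 11.4 withdraws those discovered to be ineligible at recruitment. Section 8.6 step 1 describes allocation as intention-to-treat. Suppose k such women are among 60 allocated and d others are lost. Counted as losses, attrition is (d + k)/60, so each one adds 1/60 = 1.7 percentage points overall, or 1/30 = 3.3 points within an arm of 30. Removed and replaced, they disappear from the count. The protocol does not say which treatment applies, and the value of k cannot be obtained from it.

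**The case against.** The strongest reply is that one loosely worded clause stands against three clear statements, and that other text blocks the harm. Most of this stands.

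- Section 6.3.1 says contact details are not requested at the initial screening; they are collected with the second screening. The app link goes by email, so a woman who has completed only the initial screening cannot be sent it. This does not protect against a woman who completes the second screening, falls outside its limits and has given her email address.
- Sections 8.2, 11.8 and 13.4 route women who show risk at the second screening to help pages or out of the trial. This works if allocation waits for that screening, which step 2 does not require. These routes are also described for risk, and do not cover a woman excluded because her PHQ-9 is below 5.
- Section 12.1 uses initial screening loosely, to include the suicidality exclusion that Table 8 places at the second screening. Step 2 may be equally loose. This makes 6.1 the likely intention, but does not make step 2 correct.

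A reader might infer more than the text supports:

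- **That the design randomises excluded women.** It does not; this follows only if step 2 is read alone.
- **That section 8.3 repeats the fault**, because a woman who "completes the Consent Form and is eligible for the trial, they will be given an e-mailed confirmation that they are in the study". Being eligible for the trial can mean meeting both tiers of Table 8, and 8.3 covers consent to both screenings.
- **That the WSAS has no baseline value**, because 6.1 and 8.8 name only the PHQ-9 and GAD-7. Table 9 schedules "Assessment of current functioning" at baseline and Table 12 schedules the WSAS there. Neither section says its list is complete.
- **That a given share of the 60 would be ineligible.** No second-screening failure rate appears in the protocol.

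**Conclusion.** The contradiction is real. Section 8.6 step 2 cannot be reconciled as worded with 6.1, 8.8 and Table 9, because it omits the screening that those places put before or at randomisation. The intended order is probably that of 6.1, and several provisions limit the harm, so this is a moderate fault of wording in an operating procedure and not a fatal design flaw. Its effect on the trial ranges from nothing, if 6.1 governs in practice, to the allocation of some women without the severity and suicide-risk check, if staff work from step 2. The conclusion assumes only that the numbered steps may be used as an instruction in their own right. The conflicting statements about who allocates make that plausible.

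**What to change.** Reconcile section 8.6 step 2 with 6.1, 8.8 and Table 9. State that a woman is allocated, and her download code released, only after the second screening/baseline is complete and its existing Table 8 criteria are met. Place the allocation step after the second-screening branch, and say that this holds whether Qualtrics or a member of staff performs it. Use one term for passing the initial screening and another for meeting all the criteria, so that *eligible* carries a single meaning.

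The cost is one clause, some tidying of terms and a check of the block order in Qualtrics before recruitment. No limit changes and no measure is added.
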